**METHODS::**

The study will include 30 severe TBI patients with a Glasgow Coma Scale score ≤9 who will be randomized to usual treatment, usual treatment plus early ELD placement if initial ICP ≤20 mm Hg, or late ELD if ICP ≥20 mm Hg as first intervention in tier 2 of Seattle International Brain Injury Consensus Consortium protocol.

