### Specific Aims

#### Primary Aims

To determine whether controlled CSF external lumbar drainage to reduce ICP burden after severe TBI in select patientsis associated with an increase incidence of neuroworsening events (*Safety*)can be successfully performed when indicated (*Feasibility*)

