### Randomization

The study will enroll 30 severe TBI patients who will undergo 2-stage randomization into usual treatment, usual treatment plus early ELD placement if ICP ≤ 20 mm Hg, or late ELD if ICP ≥ 20 mm Hg (Figure). The process of randomization will be centralized through a secure computerized site.

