### Outcomes

#### Primary Outcomes

Feasibility: We will calculate proportion of patients who are randomized to each intervention and receive it.Safety: Frequency of critical neuroworsening adverse events between the intervention and treatment arms as adjudicated by Data and Safety Monitoring Board (DSMB).

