## OUTCOMES

### Primary Outcomes

Both “intention-to-treat” and “treated as per protocol” analyses will be performed. Incidence of critical neuroworsening events will be compared between each arm, and between both ELD groups and control arm. Univariate and multivariable analyses will be performed using baseline variables, hourly NPI change, and volume of CSF drained per day for outcomes, ie frequency of neuroworsening events and death. Multivariable analyses will use stated adverse outcomes as dependent variables, and age group, sex, baseline ELD safety score, and pupillary abnormality as independent variables. Logistic regression will be performed using those variables that have an association with outcome with a *P*-value of ≤.10.

For feasibility, a comparison between proportion of patients in each arm who underwent ELD as per protocol will be performed. Comparison between the 2 ELD groups will be performed. Interactions will be tested for in all analyses.

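### Feasibility is defined as a within-arm proportion but analysed as between-arm contrasts of ELD receipt, which cannot show whether ELD placement succeeds

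*Protocol article*

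**What the plan says.** The Protocol article describes feasibility in three places.

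- **Specific Aims, Primary Aims.** The aim is to determine whether ELD "can be successfully performed when indicated".
- **Methodology, Outcomes, Primary Outcomes.** The outcome is a proportion for each intervention: "We will calculate proportion of patients who are randomized to each intervention and receive it".
- **Outcomes, Primary Outcomes (after Data Management and Statistical Analysis).** The analysis is a contrast: "a comparison between proportion of patients in each arm who underwent ELD as per protocol will be performed". The next sentence adds: "Comparison between the 2 ELD groups will be performed".

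In that same statistical section, the safety sentence says that the incidence of critical neuroworsening events "will be compared between each arm, and between both ELD groups and control arm".

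On design, the Randomization section states: "The study will enroll 30 severe TBI patients who will undergo 2-stage randomization into usual treatment", with the other options being "usual treatment plus early ELD placement if ICP ≤ 20 mm Hg, or late ELD if ICP ≥ 20 mm Hg". The abstract describes the late option as "late ELD if ICP ≥20 mm Hg as first intervention in tier 2" of the treatment algorithm.

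**The concern.** Whether a procedure can be carried out is a question about one group at a time: of the patients who should have received it, how many did? The outcome definition asks that question. The statistical section replaces the proportion with differences between arms, and neither difference answers it.

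If the first comparison includes usual treatment, it sets an arm assigned ELD against an arm not assigned ELD. A large difference is then expected from allocation alone, even when many placements fail. The second comparison, early against late, is silent on the level: both arms could succeed, or both could fail, with no difference between them.

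The event counted also changes. *Receiving* the intervention and having undergone ELD *as per protocol* are not the same; a drain placed late or run outside the stated limits could count under one and not the other. The aim adds a condition on indication that neither later section repeats.

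The trial is meant to inform the design of a phase 2/3 study. A feasibility result reported as a p-value between arms would tell those designers little about how often ELD can be delivered.

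**Working it through.** **Nothing to reproduce.** The article gives no power, alpha, test, precision target or allocation ratio for feasibility. The check is therefore of how the planned contrasts behave.

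**Does *each arm* include control?** Two features of the statistical section point that way. The safety sentence uses the same phrase in a passage that names the control arm. The early-versus-late comparison is also listed separately, so the preceding comparison would be redundant if it covered only the ELD arms. This is an inference; the feasibility sentence does not name control.

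**Inputs.**
- Total of 30 patients and three treatment options (Randomization section).
- Assumed: 10 per arm (30/3), with 15 ELD against 15 control as a sensitivity case.
- Assumed: Fisher's exact test, two-sided, alpha 0.05.
- Assumed: no ELD in control, since that arm is not assigned it.

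**ELD against control.** For 5/10 against 0/10, the margins are 5 ELDs among 20 patients. The two-sided p-value is 2 × C(10,5)/C(20,5) = 2 × 252/15,504 = 0.033.

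| ELD placed | Control | Success in ELD group | Fisher p |
|---|---|---|---|
| 5/10 | 0/10 | 50% | 0.033 |
| 8/20 (both ELD arms pooled) | 0/10 | 40% | 0.029 |
| 5/15 | 0/15 | 33% | 0.042 |

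Power is the sum, over all outcome pairs with p ≤ 0.05, of the binomial probabilities. With a true success rate of only 50%, the chance of a significant result is 0.62 (10 against 10), 0.87 (20 against 10) or 0.94 (15 against 15). A significant contrast is therefore compatible with poor feasibility.

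**Early against late, 10 against 10.**
- 5/10 against 5/10: p = 1.0.
- 9/10 against 9/10: p = 1.0.

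Failure in half of each arm and success in nine-tenths of each arm give the same answer. Real differences are also mostly missed: power is 0.24 for 95% against 60%, and 0.15 for 90% against 60%.

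**Within-arm estimate instead.** The exact (Clopper-Pearson) 95% limits for x of n are the 2.5% quantile of Beta(x, n − x + 1) and the 97.5% quantile of Beta(x + 1, n − x).

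| Result | Estimate | Exact 95% interval |
|---|---|---|
| 5/10 | 50% | 18.7–81.3% |
| 9/10 | 90% | 55.5–99.7% |
| 18/20 | 90% | 68.3–98.8% |

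Unlike the contrasts, this separates 5/10 from 9/10 in its point estimate and shows how uncertain each is.

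**The case against.** The strongest reply is that the right quantity is already in the plan. The Methodology outcomes section defines the per-intervention proportion, and the statistical section may only add comparisons to it. That stands. A reader might infer that the plan as a whole cannot show feasibility; it does not support that, because the proportion will be calculated and can be described. The defect is confined to the analysis given for it.

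Second, the article names no test or decision rule for feasibility, and its only p-value threshold concerns choosing variables for logistic regression. That also stands. The p-values above illustrate how the contrasts behave under stated assumptions; they are not results of a specified test, and nothing in the article says that a significant difference will be read as feasible.

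Third, control is not named in the feasibility sentence. True, but if it is excluded, only contrasts between the ELD arms remain, and these still say nothing about the level of success.

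Two further readings are tempting. One is that three different denominators are in use. In the statistical section, however, *as per protocol* qualifies the patients counted, and the base remains the patients in each arm, much as in the outcome definition. What changes there is the numerator; only the aim hints at another base. The other is that a late-ELD patient whose pressure settles before tier 2 would count as a failure among those randomized but fall outside those in whom ELD is indicated. Whether such a patient can exist depends on when the second randomization takes place, and the figure setting that out is not shown.

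Finally, the lack of a minimum acceptable feasibility rate is not an error here. The full protocol or analysis plan may state one.

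**Conclusion.** The point holds in limited form. The statistical section analyses a primary outcome through contrasts that cannot answer the stated aim, and it uses a different numerator from the outcome definition. Under the natural reading, one contrast mainly measures allocation: at an assumed 10 per arm, it reaches p = 0.033 with half the placements failing. The other returns p = 1.0 at both 5/10 and 9/10 in each arm. These figures rest on assumed arm sizes, test, alpha and counts, and on the inference that control is included. The conclusion that the contrasts do not measure feasibility does not depend on those figures and survives either reading of *each arm*. The sponsor should correct it, because feasibility is one of only two primary outcomes and the correction is cheap.

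**What to change.** Rewrite the feasibility paragraph of the statistical section so that the proportion in the Methodology outcomes section is the analysis.

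1. Choose one numerator, either receipt of ELD or ELD carried out as per protocol, define it, and use it in the aim, the outcome and the analysis.
2. Report the proportion for each ELD arm and for both pooled, among patients randomized to ELD, with an exact 95% confidence interval.
3. If the patients in whom ELD was indicated differ from those randomized to it, report the proportion among them beside the first.
4. Leave the control arm out of the feasibility analysis.
5. Keep early against late as description, without a test.

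No new data are needed. The cost is that the stated feasibility will carry a visibly wide interval: with 9/10, the lower limit is 55.5%, and with 18/20 pooled it is 68.3%. That uncertainty is already present at this sample size; the change only shows it.

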### Secondary Outcomes

Multivariable analysis will be performed using relevant clinical variables including most recent NPI before neuroworsening event, hourly change in NPI as additional independent variables introduced iteratively with neuroworsening outcomes as dependent variable.

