## METHODOLOGY

### Usual Treatment

All patients will receive usual treatment as per evidence-based guidelines and Seattle International Brain Injury Consensus Consortium (SIBICC) algorithm (Table 1).^21,22^ Either ventricular or parenchymal ICP monitors may be used. Hourly neuromonitoring will be performed including automated infrared pupillometry, GCS score, ICP, and motor examination. The NPI is an ordinal index ranging from 0 to 5, with a value of less than 3, considered abnormal pupillary reactivity based on prospective studies.^23,24^

**TABLE 1. T1:** SIBICC Treatment Algorithm

Tier 0
Admission to ICU
Endotracheal intubation and mechanical ventilation
Serial evaluations of neurological status and pupillary reactivity
Elevate HOB 30°-45°
Analgesia to manage signs of pain (not ICP directed)
Sedation to prevent agitation, ventilator asynchrony, etc. (not ICP directed)
Temperature management to prevent fever
Measure core temperature
Treat core temperature above 38°C
Consider antiseizure medications for 1 wk only (in the absence of an indication to continue)
Maintain CPP initially ≥60 mm Hg
Maintain Hb >7 g/dL
Avoid hyponatremia
Optimize venous return from head (eg, head midline, ensure cervical collars are not too tight)
Arterial line for continuous blood pressure monitoring
Maintain SpO_2_ ≥94%
Recommended interventions
Insertion of a central line
End-tidal CO_2_ monitoring
Tier 1
Maintain CPP 60-70 mm Hg
Increase analgesia to lower ICP
Increase sedation to lower ICP
Maintain PaCO_2_ at low end of normal (35-38 mm Hg/4.7-5.1 kPa)
Mannitol by intermittent bolus (0.25-1.0 g/kg)
Hypertonic saline by intermittent bolus
CSF drainage if EVD in situ
Consider placement of EVD to drain CSF if parenchymal probe used initially
Consider antiseizure prophylaxis for 1 wk only (unless indication to continue)
Consider EEG monitoring
Tier 2
Mild hypocapnia range 32-35 mm Hg/4.3-4.6 kPa
Neuromuscular paralysis in adequately sedated patients if efficacious
Perform MAP Challenge to assess cerebral autoregulation and guide MAP and CPP goals in individual patients
Should be performed under direct supervision of a physician who can assess response and ensure safety
No other therapeutic adjustments (ie sedation) should be performed during the MAP Challenge
Initiate or titrate a vasopressor or inotrope to increase MAP by 10 mm Hg for not more than 20 minutes
Monitor and record key parameters (MAP, CPP, ICP, and PbtO_2_) before during and after the challenge

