#### Secondary Outcomes

Association of absolute NPI and between-eyes NPI difference with.ELD safety score on screening CT head,Temporal occurrence of neuroworsening events.

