## SAFETY CONSIDERATIONS

### Risks to Human Subjects

Critical neuroworsening events related to ELD and CSF drainage are neurological worsening events such as decrease in GCS score, development of new motor deficit, or a cerebral herniation event, and rarely death (Table 2). Given the greatest risk of neuroworsening from herniation is soon after drainage is commenced, all patients will have neurological checks ie GCS score, ICP measurement, automated pupillometry for pupillary size, symmetry and NPI performed every 15 minutes for 1 hour after ELD placement, and start of CSF drainage. If NPI drops <3 within the first hour, a head CT may be obtained to review any craniocaudal shift. After the first hour, measurements will be performed hourly.

**TABLE 2. T2:** Neuroworsening Events

Critical neuroworsening events per SIBICC protocol
1. Spontaneous decrease in the GCS motor score of ≥1 points (compared to previous exam)
2. New decrease in pupillary activity
3. New pupillary asymmetry or bilateral mydriasis
4. New focal motor deficit
5. Herniation syndrome or Cushing Triad which requires an immediate physician response

GCS, Glasgow Coma Scale.

Based on inclusion/exclusion criteria, we analyzed the severe TBI BTF-New York State TBI-trac database from 1997 to 2007, with 1100 patients. The inclusion criteria applied to 47% of all severe TBI patients admitted over 10 years to 11 level 1 trauma centers in the state; 22% (95% CI: 19.9%-24.3%) suffered new pupillary asymmetry at any point during admission, 18% (95% CI: 12.6%-25.0%) suffered new motor deficit, and 22.4% (95% CI: 20.2-24.8) experienced death at 2 weeks.

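### NPI is tested against a composite in which two of the five events are themselves pupillary, and one of its predictors has no value for patients without an event

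*Protocol article*

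**What the plan says.** The Secondary Aims (Protocol article) have two NPI parts: whether NPI correlates with the ELD safety score, and whether NPI falls ahead of any critical neuroworsening event. The Secondary Outcomes list under Methodology matches this, with "Association of absolute NPI and between-eyes NPI difference" set against the screening CT safety score and against the timing of neuroworsening.

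Table 2 (Risks to Human Subjects) defines the critical neuroworsening events. Two of its five items are "New decrease in pupillary activity" and "New pupillary asymmetry or bilateral mydriasis". The others are a fall in GCS motor score, a new focal motor deficit, and a herniation syndrome or Cushing triad.

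Usual Treatment describes NPI as an index from 0 to 5, "with a value of less than 3, considered abnormal pupillary reactivity". Risks to Human Subjects takes pupil size, symmetry and NPI from the same automated device.

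The Secondary Outcomes section that follows Data Management and Statistical Analysis plans a multivariable model with "most recent NPI before neuroworsening event, hourly change in NPI as additional independent variables introduced iteratively with neuroworsening outcomes as dependent variable". The Primary Outcomes section just before it also relates hourly NPI change to the frequency of neuroworsening. On size, the Randomization section says: "The study will enroll 30 severe TBI patients who will undergo 2-stage randomization".

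**The concern.** A predictor should not share its definition with the outcome it is meant to predict. Here a fall in pupillary reactivity, or a new difference between the eyes, can appear on both sides of the model: as a change in NPI and as a Table 2 event. Part of any association found would then come from the definitions and say nothing about prognosis.

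The second problem is one of construction. A covariate defined as the last reading before an event has a value only in patients who had one.

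The stated purpose of the aim is to learn whether routine pupillometry can serve as a safety tool for ELD. For that, the useful question is whether NPI gives notice of herniation or motor decline that has not yet happened. The analysis as written cannot separate that from pupillometry agreeing with itself.

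**Working it through.** The article gives no power or precision figure for this analysis, so there is none to reproduce. The check is a comparison of definitions, followed by simple counts.

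**1. Outcome against predictors**

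| Table 2 event | Overlap with an NPI term? |
|---|---|
| 1. Fall in GCS motor score | No |
| 2. Decreased pupillary activity | Yes: NPI is an index of pupillary reactivity |
| 3. New asymmetry or bilateral mydriasis | Yes in part: between-eyes NPI difference is closely related, although asymmetry can also be one of size |
| 4. New focal motor deficit | No |
| 5. Herniation syndrome or Cushing triad | Possible, where pupillary signs establish it |

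The Inclusion Criteria require symmetric, bilaterally reactive pupils at entry. A later fall of NPI into the abnormal range is therefore, on a plain reading, a new decrease in reactivity. Nothing in the article removes items 2 and 3 from the outcome of the NPI model, and the aim refers to any critical event.

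**2. Which NPI terms are affected**

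- Hourly change and between-eyes difference: most affected. No lag is set and the event-time reading is not excluded, so the change entered can be the event itself.
- Last reading before the event: less affected, since it is a different measurement. For a sudden pupillary event that reading would be normal, which pulls towards no association, so the direction of bias is not fixed.
- NPI against the ELD safety score: not affected.

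**3. Patients with no value for the last reading before an event**

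Inputs from Risks to Human Subjects: new pupillary asymmetry 22%, new motor deficit 18%. Assume that these historical rates apply to the 30 trial patients and that only these two event types occur.

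- No overlap: 30 × (1 − 0.22 − 0.18) = 18.0
- Independent: 30 × 0.78 × 0.82 = 19.2
- Full overlap: 30 × (1 − 0.22) = 23.4

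So about 18 to 23 of 30 patients would lack the covariate. Other Table 2 events would lower these counts.

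**4. Events left if pupillary ones are removed**

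Motor deficits: 30 × 0.18 = 5.4. Over the quoted interval of 12.6% to 25.0%, this is 30 × 0.126 = 3.8 to 30 × 0.25 = 7.5. Declines in GCS motor score would add to this, but the article gives no rate for them.

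**5. Illustration of the mechanism**

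In a simulation of 4,000 trials of 30 patients (Fisher exact test, two-sided 0.05), an NPI fall was made to coincide with a pupillary event and to carry no information about motor deficit. NPI was significant against the composite in 98% of trials with pupillary events at 22%, 72% at 10% and 35% at 5%. Against motor deficit alone it was significant in about 1 to 2%. The coincidence is assumed, so this shows what full overlap would do. It does not estimate the bias in this trial.

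**The case against.** Several points on the other side hold.

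- A reader might infer that the whole NPI aim is circular. It is not: the ELD safety score is read from CT and is independent of pupillometry.
- A reader might infer that a strong association is guaranteed. The documents do not support that. Table 2 names no NPI threshold, the article lists size, symmetry and NPI as separate measurements, the aim asks about NPI before the event, and a strictly earlier reading is not the event. The simulation above assumes coincidence and cannot settle this.
- A reader might take 22/(22 + 18) = 55% as the share of events that are pupillary. That uses two of five event types, assumes that they never overlap, and rests on patient-level rates from 1997 to 2007. The article gives no rates for declines in GCS motor score or for herniation syndrome, so the share is unknown.
- A condensed article may leave index time, lag, clustering and order of entry to the analysis plan. Their absence is not the point here. Hourly change in NPI exists for every patient, and the plural wording for the outcome leaves room for analysis by event type.
- The phase 2/3 decision in Expected Outcomes of the Study rests on serious adverse events, and the NPI stop criterion is already set, so the wider consequence is limited.

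What survives is what the article itself fixes: an outcome that includes pupillary events, and a covariate conditional on the event. Room to analyse by event type is not a plan to do so.

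**Conclusion.** The concern holds for the NPI-versus-neuroworsening part of the secondary aim only. That part is partly circular: two of the five outcome items overlap with the NPI terms, most clearly with hourly change and between-eyes difference. An association with the composite would not show that NPI warns of herniation or motor decline. The size of the distortion cannot be derived from the article.

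The last-reading covariate is undefined for event-free patients, roughly 18 to 23 of 30 under the two-event assumption, so the model cannot be fitted as written to patients with and without events. This is a correction worth making to a secondary analysis. It does not affect the primary comparison of event incidence between arms.

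**What to change.** In the Secondary Outcomes section of the statistical analysis:

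- Make non-pupillary events the outcome of the NPI analysis: Table 2 items 1 and 4, and item 5 when established without pupillary signs. Report pupillary events separately.
- Replace the last NPI before an event with time-updated NPI in all patients. Use only readings taken strictly before the event assessment, and allow for repeated readings within patient.
- Keep the 15-minute readings from the first hour after ELD. A blanket lag of an hour or more would discard them in the period that the article itself calls the time of greatest herniation risk.

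The hourly and 15-minute readings are already planned, so no new data are needed. The cost is precision. With about 5 motor deficits expected, plus any declines in GCS motor score, intervals will be wide, multivariable modelling will be fragile, and the result should be read as descriptive.
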